### Recruitment

Participants will be recruited in 13 hospitals (Supplementary File 2). Patients willing to participate in the trial will be screened for eligibility by a clinical researcher. Eligible patients will receive detailed information about the clinical trial. Patients providing consent to the clinical study terms will participate in the trial and will be randomly assigned to the QDG or control group.

### Randomization and blinding

Participants will be randomized in a 1:1 ratio to the QDG or control group using a computer-generated, site-stratified, block randomization schedule. The study drugs will be labeled with sequential randomization numbers, and the participant will be assigned the lowest number available at each hospital. All participants, care providers, and attending physicians will be blinded to the assignment until the trial is finished. The trial-group assignment will be concealed from all participants, clinicians, and investigators throughout the trial. To ensure blinding, randomization sequences will be generated by statisticians and then kept in identical, opaque, sealed, sequentially numbered envelopes. Only the trial’s pharmacist has access to the randomization list.

### Intervention

The course of treatment will last 4 weeks, and patients will be followed up for 4 additional weeks to assess any persistent effects of the drug. Participants will be examined at week 0 (baseline, visit 2), week 4 (end of treatment, visit 3), and week 8 (end of follow-up, visit 4). The QDG group will be treated with valsartan capsule simulation agent (80 mg, once daily for 4 weeks) and QDG (5 g, twice daily for 4 weeks), while the control group will be treated with valsartan capsule simulation agent (80 mg, once daily for 4 weeks) and QDG simulation agent (5 g, twice daily for 4 weeks). The drugs and simulation agents will be provided by Jiangyin Tianjiang Pharmaceutical (Jiang’yin City, China). The simulation agent will be prepared using soluble starch, colorant, and a bitter additive to achieve appearance, smell, and taste comparable to the drug. The drugs and simulation agents will be identical in outer packaging, color, shape, and flavor. The drug that patients did not take would be returned to the researcher. And no other anti-hypertension drugs should be taken during the study process.

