**Methods:**

The study is designed as a randomized, multi-center, double-blinded, non-inferiority clinical trial. Five hundred fifty-two patients with grade 1 hypertension at low-medium risk from 13 hospitals will be recruited and randomly assigned to the QDG group (*n* = 276, treated with valsartan capsule simulation agent and QDG) or control group (*n* = 276, treated with valsartan capsule and QDG simulation agent). The treatment period will be 4 weeks and the follow-up period will last 4 weeks after treatment. Primary outcome will be a decreased value of systolic blood pressure and diastolic blood pressure after treatment. And second outcome will include the decreased value of diastolic blood pressure and systolic blood pressure at the end of follow-up, the percentage of participants achieving normal blood pressure at the end of treatment and follow-up, the Hamilton Anxiety Scale and TCM syndrome scores at the end of treatment and follow-up, and levels of hypertensive hormones at end of treatment and follow-up.

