## Background

About 1.13 billion individuals suffer from hypertension around the world, with fewer than 20% of them being controlled to normal blood pressure [1]. Previous studies demonstrated that hypertension could increase the risk of coronary heart disease, stroke, and end-stage renal disease [2–4]. Although antihypertensive drugs are effective in treating hypertension and decreasing hypertension-associated risks, the side effects of these drugs often result in the discontinuation of the prescription [5, 6].

Traditional Chinese medicine (TCM) has shown efficacy in treating hypertension without severe side effects [7]. In particular, *Qingxuan Jiangya* decoction (QXJYD) has been used for the treatment of hypertension for many years in clinical practice [8]. QXJYD can decrease blood pressure and arterial vascular remodeling in spontaneously hypertensive rats [8, 9].

*Qingda* granule (QDG) formulation, simplified from QXJYD. The main drug components include *Gastrodia elata*, *Uncaria*, *Scutellaria baicalensis*, and lotus germ, which were shown to attenuate elevated blood pressure and promote vasorelaxation of thoracic aortic rings in the animal study with spontaneously hypertensive rats [10]. Some QDG components such as rhynchophylline, gastrodin, and baicalin have antihypertensive effects [9, 11, 12]. These findings have provided important evidence to further validate the anti-hypertensive effects of QDG in clinical trials. In the currently multi-center, double-blinded, randomized controlled non-inferiority trial, the objective is to evaluate the effects and safety of QDG compared with valsartan.

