### Sample size

The target sample size was calculated according to the decreased value of systolic blood pressure (12.9±11.8 mm Hg) observed after 8-week treatment with valsartan capsules in a randomized clinical trial [16], and the non-inferiority margin of QDG has been established as −3 mm Hg. The decreased value of QDG on systolic blood pressure was 12.0±10.5 mm Hg, which was calculated based on our clinical practice. The minimal sample size to achieve a type I error rate of *α* = 0.05 and a power of 80% (type II error rate *β* = 0.2) is 440 participants. The size was calculated using the formula:$$n=\frac{{\left({Z}_{1-\alpha }+{Z}_{1-\beta}\right)}^2\times \left({\upsigma}_1^2+{\upsigma}_2^2\right)}{{\left(\varepsilon -\delta \right)}^2}$$where σ_1_ and σ_2_ are the standard deviations of the QDG and control groups, respectively; *ε* is the mean difference between the two groups; δ is the non-inferiority margin; *α* is the type I error rate; and *β* is the type II error rate. The study will strive to enroll 550 participants to compensate for a dropout rate as high as 20%. For convenience of randomization, we will aim to recruit 552 patients.

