## Discussion

QXJYT was created by Academician [name]. After years of clinical practice, it has been proved to have a certain antihypertensive effect, which can significantly improve the clinical symptoms and quality of life of hypertension. At the same time, it has an obvious protective effect on target organs [17]. QDG is composed of *Gastrodia elata*, *Uncaria*, *Scutellaria baicalensis*, and *lotus seed heart* according to more than 60 years’ clinical experience of Academician [name] in addition and subtraction of QXJYT [18]. In the present clinical trial, the effects of QDG on grade 1 hypertension (low-medium risk) will be investigated. QDG, derived from QXJYD, showed obvious effects on decreasing blood pressure and promoting the vasorelaxation of thoracic aortic rings in spontaneously hypertensive rats [10]. Further mechanistic investigation demonstrated that QDG ameliorated Ang II-induced hypertension in mice and inhibited proliferation of vascular smooth muscle cell of aorta via suppressing the activation of MAPKs and PI3K/AKT pathways [19]. In addition, some components of QDG, such as rhynchophylline, gastrodin, and baicalin, also have the effects of antihypertension [9, 11, 12]. These results serve as a solid foundation for the present clinical trial investigating the effects of QDG on grade 1 hypertension with low-medium risk. The present clinical study is designed as a randomized, multi-center, double-blinded, placebo-controlled, non-inferiority trial, which will provide high-quality evidence for the further clinical practice of QDG.

The clinical trial will be performed in China and will enroll Chinese patients, and the 13 hospitals will mainly serve Han Chinese, so it will not evaluate the effects of QDG in other ethnic groups. The follow-up period is relatively short, and therefore, some effects may be potentially missed.

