## Trial status

The trial is currently in the status of data analysis. The study started recruiting participants in May 2020 and ending in December 2021. The protocol version number is ChiCTR2000033890 and the date is June 15, 2020. The protocol has been submitted in October 2020; unfortunately, the manuscript was submitted as a research article but it has since been identified as a Study Protocol article. The journal found the question after 2 years and required us to re-submit the manuscript in September 2022. So the manuscript was published late.

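### The Intervention section gives the control group dummy valsartan, contradicting the abstract, the objective and the sample size; probably a drafting slip, but in the only section that gives doses

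*Protocol article*

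**What the plan says.** The Intervention section of the protocol article sets out both regimens. For the experimental arm: "The QDG group will be treated with valsartan capsule simulation agent (80 mg, once daily for 4 weeks) and QDG (5 g, twice daily". For the control arm: "while the control group will be treated with valsartan capsule simulation agent (80 mg, once daily for 4 weeks) and QDG simulation agent". It describes the simulation agent as starch with colorant and a bitter additive, that is, a placebo, and adds that "no other anti-hypertension drugs should be taken during the study process".

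Other sections describe a different control arm:

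- Abstract, Methods: the control group is "treated with valsartan capsule and QDG simulation agent".
- Background: "the objective is to evaluate the effects and safety of QDG compared with valsartan".
- Sample size: the control response of 12.9 (SD 11.8) mm Hg is the one "observed after 8-week treatment with valsartan capsules in a randomized clinical trial", and a non-inferiority margin of −3 mm Hg is set against it.

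The Discussion calls the study a "placebo-controlled, non-inferiority trial". The Trial status section reports: "The trial is currently in the status of data analysis".

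**The concern.** Read as written, the Intervention section gives the valsartan dummy to both arms. The control arm then has two placebos, and no participant takes valsartan. That cannot be reconciled with the abstract, the objective or the sample-size basis.

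The identity of the comparator decides what a non-inferiority result means. If valsartan was in fact dispensed, the article misdescribes its control arm in the section readers will use to learn what was given. No section then states a dose for active valsartan, because the 80 mg is attached only to the dummy. If valsartan was not dispensed, lying within 3 mm Hg of placebo says nothing about QDG against valsartan, and controls had no antihypertensive drug by design during the 4-week treatment period.

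**Working it through.** **Step 1. Compare the sections.**

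| Section | QDG arm | Control arm |
|---|---|---|
| Abstract, Methods | valsartan dummy + QDG | active valsartan + QDG dummy |
| Background (objective) | QDG | valsartan |
| Sample size | QDG, decrease 12.0 (SD 10.5) | valsartan, decrease 12.9 (SD 11.8) |
| Intervention | valsartan dummy + QDG | valsartan dummy + QDG dummy |

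Only the Intervention section departs from the rest, and only in one component of one arm.

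**Step 2. Which reading is more likely?** A valsartan dummy in the QDG arm has a purpose only if the other arm takes real valsartan. If nobody took valsartan, the capsule would be pointless in both arms. The abstract's pairing is the standard double-dummy arrangement. The likely explanation is that the words for the dummy capsule were repeated from the QDG clause. The Discussion's placebo-controlled label is loose wording and is not independent evidence of a placebo comparator.

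**Step 3. Does the correction alter the plan's numbers?** No. The Sample size section already assumes a valsartan control, so its inputs stay as they are. The dropout step reproduces: 440 / 0.8 = 550. The figure of 440 does not follow from the stated inputs. With one-sided alpha 0.05, 80% power and a true difference of −0.9, the formula gives (1.645 + 0.842)² × (11.8² + 10.5²) / (−0.9 + 3)² ≈ 350 per arm, 700 in total. That is a separate matter and has no bearing on this one.

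**Step 4. What if the Intervention section were literally true?** Suppose QDG is inert, so that both arms are inert and the true systolic difference is 0.

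- Inputs: SDs 11.8 and 10.5 and margin 3 mm Hg (Sample size); n = 220 per arm (440 evaluable) or 276 per arm (all randomised).
- Alpha: the Sample size section uses 0.05 with a one-sided quantile; the Statistical analysis section uses two-sided tests at p < 0.025. One-sided 0.05, 0.025 and 0.0125 are therefore all shown.
- Standard error: SE = √((11.8² + 10.5²)/n) = √(249.49/n), which is 1.065 at n = 220 and 0.951 at n = 276.
- Probability of meeting the criterion: Φ(3/SE − z).

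| One-sided alpha (z) | n = 220 per arm | n = 276 per arm |
|---|---|---|
| 0.0125 (2.241) | 0.718 | 0.820 |
| 0.025 (1.960) | 0.804 | 0.884 |
| 0.05 (1.645) | 0.879 | 0.935 |

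For example, at n = 220 and z = 2.241: 3/1.065 − 2.241 ≈ 0.576, and Φ(0.576) ≈ 0.718.

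The article gives no SD for untreated patients. With an assumed common SD of 14 (n = 220, z = 2.241) the probability is 0.502. With an assumed common SD of 10 (n = 276, z = 1.645) it is 0.970. The calculation covers systolic pressure only, because no diastolic margin or SD is given.

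**The case against.** The strongest reply is that this is an erratum and no more. The abstract states both arms clearly and symmetrically, and the objective and sample size agree with it, so a reader of the whole article would not conclude that the comparator was placebo. The Intervention section itself leans the same way: it bars *other* antihypertensives, which suggests participants already receive one; it speaks of study drugs in the plural; and it gives a dose of 80 mg, as for a real capsule. On that reading the numerical effect is nil. The probabilities above then quantify the less plausible branch, with SDs borrowed from active treatment. The Withdrawal, dropout, and discontinuation section also foresees added antihypertensives for participants who progress to grade II or III. Finally, the flow chart is not visible here and the full protocol, available on request, may be right.

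Much of this stands. A slip is the better explanation, the calculation does not decide the point, and the wording of the Discussion is secondary. What is established is an error in the published article, not in what patients took. Three things do not go away. The wrong statement is in the one section that specifies treatment. Nothing visible in the article corrects it. The added-drug provision covers only participants who progress, so it does not put valsartan back into the control arm.

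**Conclusion.** The concern holds and must be fixed. The control regimen in the Intervention section is wrong as written and conflicts with the abstract, the objective and the sample-size basis.

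- **If active valsartan was dispensed (probable):** no effect on design, sample size or analysis; the control arm is misdescribed.
- **If it was not:** non-inferiority to valsartan cannot be concluded. An inert granule would satisfy the −3 mm Hg systolic criterion with probability 72% to 93% across the alphas and arm sizes considered, or 50% to 97% if the common SD may lie anywhere from 10 to 14 mm Hg. These figures rest on a true difference of 0 and on assumed SDs for inert arms.

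The priority comes from where the error sits and what it concerns, not from a claim that placebo was actually given.

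**What to change.** Before results are reported, check the content of the control kits against the approved full protocol and the drug-kit and dispensing records.

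- **If they show active valsartan:** correct the control regimen in the Intervention section to an active valsartan capsule, 80 mg once daily, plus QDG simulation agent, 5 g twice daily, both for 4 weeks. As a secondary edit, describe the trial in the Discussion as active-controlled and double-dummy.
- **If they show that active valsartan was not dispensed:** draw no non-inferiority conclusion against valsartan.

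The cost is a text change in two places and a look at existing records. It does not depend on the blind, so it can still be done although the trial has reached data analysis.

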### Outcomes assessment

#### Primary outcome

After 4 weeks’ treatment, the decreased values of clinic systolic blood pressure and diastolic blood pressure after treatment are used as primary outcome (the difference between visits 3 and 2). Clinic blood pressure was measured using an automated sphygmomanometer (Omron, HEM-7121) in the right arm with an appropriate cuff size. The measurements were taken after the participants rested in a sitting position for 5 min, at least 1 h after the subject’s last meal, and at least 30 min after smoking or consuming caffeinated beverages. To obtain accurate data, the measurements will be conducted 3 times, and the mean value will be used as the outcome.

#### Secondary outcomes

The decreased value of clinic systolic and diastolic blood pressure after 4-week follow-up (the difference between visits 4 and 2).The percentage of participants achieving normal clinic blood pressure (systolic blood pressure ≤120 mm Hg and diastolic blood pressure ≤80 mm Hg) by the end of treatment (visit 3) and at the end of follow-up (visit 4).The mean systolic/diastolic blood pressure during 24-h, daytime, and nighttime at the end of treatment (visit 3) and end of follow-up (visit 4).The Hamilton Anxiety Scale and TCM syndrome scores at the end of treatment (visit 3) and end of follow-up (visit 4).Levels of hypertensive hormones (renin, aldosterone, cortisol, and corticotropin) at the end of treatment (visit 3) and end of follow-up (visit 4).

Clinic blood pressure will be measured as described above. Ambulatory blood pressure monitoring was performed using validated oscillometric monitors (Meditech, ABPM-05). And hypertension hormone (renin, aldosterone, cortisol, and corticotropin) will be collected in the morning fasting after lying down for 1-h venous blood, using the immunoassay.

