**Fig. 1 Fig1:**
[figure not shown]
SPIRIT schedule of enrolment, interventions, and assessments. Abbreviations: MACCEs, major adverse cardiac and cerebrovascular events; TCM, traditional Chinese medicine

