### Statistical analysis

The data analysis will be based on the principle of intention to treat (ITT), and potential missing values will be filled in using data from the last observation. Data will be presented as mean ± standard deviation, median with range, or number and percentage. Data will be analyzed using SAS 9.3 software (SAS Institute, Cary, NC, USA) using two-sided tests and a significance level of *p* < 0.025. For comparison between groups, two independent sample *T*-test (group *T*-test ) and Wilcoxon rank sum test were used for measurement data. The Pearson chi-square test or Fisher exact test was used for counting data. Wilcoxon rank sum tests were used for grade data. For intra-group comparison, paired *T*-tests or Wilcoxon symbolic rank test was used for measurement data. CMH chi-square tests were used when considering the central effect. Sub-group analyses will be conducted based on the characteristics of included participants.

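### The stated between-arm tests for ambulatory pressure, anxiety, TCM and hormone outcomes are unbiased but leave the visit-2 value unused; adjusting for it would give tighter estimates from the same patients

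*Protocol article*

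**What the plan says.** The Secondary outcomes list uses two kinds of definition.

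- Clinic pressure is anchored to baseline: "The decreased value of clinic systolic and diastolic blood pressure after 4-week follow-up (the difference between visits 4 and 2".
- The other continuous outcomes are values at the two later visits. Ambulatory pressure is "The mean systolic/diastolic blood pressure during 24-h, daytime, and nighttime at the end of treatment (visit 3) and end of follow-up (visit 4". Both scales are "The Hamilton Anxiety Scale and TCM syndrome scores at the end of treatment (visit 3) and end of follow-up (visit 4". The hormones are "Levels of hypertensive hormones (renin, aldosterone, cortisol, and corticotropin) at the end of treatment (visit 3) and end of follow-up (visit 4".

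On analysis, the Statistical analysis section says that between groups "two independent sample *T*-test (group *T*-test ) and Wilcoxon rank sum test were used for measurement data". It names no baseline covariate. Within groups it says: "For intra-group comparison, paired *T*-tests or Wilcoxon symbolic rank test was used for measurement data".

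On timing, the Intervention section says: "Participants will be examined at week 0 (baseline, visit 2), week 4 (end of treatment, visit 3), and week 8 (end of follow-up, visit 4". No sentence lists what is measured at visit 2 for these outcomes. That belongs to Fig. 1, captioned "SPIRIT schedule of enrolment, interventions, and assessments", which is not shown in the copy reviewed.

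**The concern.** Taken together, the outcome definitions and the named tests compare raw visit 3 or visit 4 values between arms. For clinic pressure the baseline enters by subtraction. For the ambulatory pressures, the two scales and the four hormones it does not enter the between-arm comparison at all, although the paired tests suggest that it was measured.

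Two things are at stake. The first is precision: stable differences between patients stay in the error term when a baseline value could remove part of them. The second is what may be claimed. The comparator is active, so similar week-4 ambulatory pressures in the two arms do not by themselves show that pressure fell in either. A statement about reduction needs the visit-2 value.

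**Working it through.** The plan gives no sample size, standard deviation, power or correlation for these outcomes, so there is no figure of its own to reproduce. The check compares three analyses of the same data.

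**Inputs**

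- Allocation is 1:1 and randomised (Randomization and blinding).
- The between-arm tests are the two named under Statistical analysis, two-sided at 0.025.
- n = 220 per arm is half of the stated minimum of 440 (Sample size). It is used only to give scale, and nothing here depends on how 440 was derived.
- r, the correlation between the visit-2 value and the later value, is not in the documents. It is assumed to lie between 0.3 and 0.7.

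**Formulas.** Let σ be the between-patient SD, equal at both visits, with n patients per arm. The variance of the arm difference is:

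- raw later value: 2σ²/n, relative variance 1
- change from visit 2: (2σ²/n) × 2(1 − r), relative variance 2(1 − r)
- later value adjusted for visit 2 (ANCOVA): (2σ²/n) × (1 − r²), relative variance 1 − r²

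Confidence interval width scales with the square root of the relative variance.

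**Results**

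| r (assumed) | Change score, 2(1 − r) | ANCOVA, 1 − r² | ANCOVA variance saving | ANCOVA interval width, √(1 − r²) | Interval narrower by |
|---|---|---|---|---|---|
| 0.3 | 1.40 | 0.91 | 9% | 0.954 | about 5% |
| 0.5 | 1.00 | 0.75 | 25% | 0.866 | about 13% |
| 0.7 | 0.60 | 0.51 | 49% | 0.714 | about 29% |

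The saving at r = 0.7 is 1 − 0.51 = 0.49, so the variance falls to 51% of its unadjusted value.

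**Scale.** The difference detectable with 80% power at two-sided 0.025, in SD units, is (2.241 + 0.842) × √(2/220) × √(relative variance) = 0.294 × √(relative variance).

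| r (assumed) | Raw value | Change score | ANCOVA |
|---|---|---|---|
| 0.3 | 0.294 | 0.348 | 0.280 |
| 0.5 | 0.294 | 0.294 | 0.255 |
| 0.7 | 0.294 | 0.228 | 0.210 |

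**Reading the tables.** ANCOVA lowers the variance at any non-zero r. A change score beats the raw value only when r exceeds 0.5, equals it at 0.5, and is worse below that (variance up 40% at r = 0.3). Redefining these outcomes as differences from visit 2 and applying the named t-test could therefore lose precision. The formulas describe the t-test case in large samples. For outcomes analysed by the rank sum test the gain is only indicative. Any further gain from adjusting for site is not counted.

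**The case against.** The strongest reply is that nothing here is an error. A value at the end of treatment is a valid endpoint, and randomisation makes its comparison between arms unbiased. Chance baseline imbalance adds variance, which the standard error already reflects. An outcome defined at visit 3 does not exclude baseline as a covariate. The covariates may be set in the full protocol or analysis plan, and the article names no adjustment for clinic pressure either. Most of this stands. What remains is that the article does name the between-arm tests, and those tests, applied to these definitions, use no baseline.

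Three stronger readings are tempting, and the documents do not support them.

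- A reader might infer that no baseline was planned for these measures. The text does not say so. There is a week-0 examination, paired tests presuppose an earlier value, and the assessment schedule is in a figure not shown here.
- A reader might infer that the outcomes cannot show change, or that the only possible pair is visit 3 against visit 4. Both depend on visit-2 values being absent, which is not established, and no section proposes that pair as evidence of effect.
- A reader might add that hospital-to-hospital laboratory differences inflate the hormone comparison. The laboratory arrangement under Safety follows a sentence on hepatic and renal samples, hormone sampling is described separately, and randomisation is stratified by site.

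**Conclusion.** The point holds as a matter of efficiency and of the wording of claims, not of bias. For these secondary outcomes the stated between-arm comparison is valid but leaves out the visit-2 value that the paired tests imply. With r assumed between 0.3 and 0.7, baseline adjustment brings the variance of the arm difference to between 0.91 and 0.51 of its unadjusted value, with intervals about 5% to 29% narrower. The size rests on that assumed r and on visit-2 values having been collected. If they were not, there is no precision to recover, and only the limit on claims of reduction remains. The primary outcome is not affected.

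**What to change.** - Confirm from the assessment schedule which of these measures were taken at visit 2, and say so in the text.
- Where a visit-2 value exists, keep the visit 3 and visit 4 values as the outcomes. Compare arms by ANCOVA with the visit-2 value and site as covariates, with skewed hormones on the log scale (baseline logged as well). Use this in place of the unadjusted test, and do not substitute a plain change score.
- Where no visit-2 value exists, report a post-treatment comparison between arms only, with no claim of reduction from baseline.

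The cost is small: a few lines of text and a change of model, with no new data. The Trial status section puts the trial at data analysis, so the change should be fixed and dated before the arm comparisons for these outcomes are examined. If they have already been seen, the adjusted analysis should be labelled as added afterwards and shown beside the unadjusted one.
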